#### Sample size

Previous studies have estimated that 3–38% of adolescents suffer from chronic pain. Assuming that 25% of our sample have chronic pain, this suggests that for a total of 288 responses, 95% confidence limits will be 20% and 30% with a precision of 5% (Sample size for prevalence surveys, © 2003–2005 Philippe Glaziou). With an estimated response rate of 80%, it is aimed to include 360 adolescents. The calculation is based on a population size of 86424 adolescents between 11 and 17 years in central part of Switzerland (canton Luzern, Aargau, Schwyz and Zug) in 2021.

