### Setting

Participants will be recruited from primary, secondary and high schools in the cantons of Lucerne, Zug, Schwyz and Aargau, that is from the German speaking region in Central Switzerland. There is no evidence for different pain prevalence compared to other German-speaking cantons in Switzerland. All participating schools will be mixed/single gender, publicly funded and non-fee paying, and located in a mix of urban and rural areas of Central Switzerland. Study participants with an age range between 11 and 17 years will be recruited from participating schools. Currently, four schools with about 400 possible adolescents have provisionally confirmed their participation.

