### Data collection

The PI (HS) will be present in the classroom together with the teacher to administer the link to the questionnaires or reading substitute task to all adolescents. This also ensures that direct enquiries can be made and compliance with the study protocol. Excluded children adolescents receive help from HS and the teacher to decide on the substitute task. Participating adolescents will be invited to complete questionnaires related to i) their demographics (age, gender, class grade), ii) the absence/presence of chronic pain, iii) pain characteristics and impact (those with chronic pain only), and iv) knowledge and beliefs about pain. The demographic data and the pain-related questionnaires will be completed via the cloud-based survey tool LimeSurvey. Piloting the questionnaires ensured that the questions were comprehensible and took approximately ten minutes to answer.

During the data collection period anonymised data will be stored digitally in the LimeSurvey cloud and will be accessible to the research team only. After each data collection session the data will be exported to and stored in a password protected folder on the Haute École de Santé Vaud in Switzerland for ten years. All data will be handled in accordance with current Swiss legislation [36]. On completion of the study we will make our anonymised data available without restriction on the Open Science Framework [35].

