### Statistical analysis plan

Data will be entered, cleaned, and analysed using the Statistical Packages for the Social Sciences (SPSS), currently version 27. An estimate of the point prevalence of chronic pain will be reported, with a 95% confidence interval. Adolescents’ demographics, pain characteristics, PROMIS-PPIS and COPI-GER scores will be reported for the entire cohort and according to presence/absence of chronic pain, age and gender using standard descriptive statistics. Continuous data will be reported using mean scores, ranges, and standard deviations. Logistic regression models will be constructed to first establish the association between the presence of chronic pain, including PROMIS-PPIS and demographic factors (age, gender). Next the relationship between chronic pain and total COPI-GER score as well as individual items in the child’s COPI-GER, independent of age and gender, will be explored with logistic regression models. Results will be expressed as odds ratios.

Linear regression models will be used to explore the association between the pain interference (PROMIS-PPIS) and the pain knowledge and beliefs (COPI-GER) in adolescents with and without chronic pain, with further analysis by age and gender. Sensitivity analyses will be performed to assess the robustness of the results, such as excluding participants or outliers.

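### The ±5-point precision from 288 responses holds only under simple random sampling, but pupils enter in class groups from about four schools

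*Protocol article*

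**What the plan says.** **Sample size.** The calculation starts from "Assuming that 25% of our sample have chronic pain" and concludes that "for a total of 288 responses, 95% confidence limits will be 20% and 30% with a precision of 5" percent. It then says: "With an estimated response rate of 80%, it is aimed to include 360 adolescents". The finite population is given: "The calculation is based on a population size of 86424 adolescents between 11 and 17 years". No design effect, ICC or number of clusters is mentioned.

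**Setting, Recruitment and Data collection.** At the time of writing, "four schools with about 400 possible adolescents have provisionally confirmed their participation". Schools are approached first, teachers then agree to help, and they introduce the study to their pupils in lesson time. The principal investigator attends the classroom and gives the survey link to everyone there; pupils may choose a reading task instead. The questionnaire opens with "their demographics (age, gender, class grade"). Neither that list nor the one under Outcome measures names a school or class identifier.

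**Statistical analysis plan.** "An estimate of the point prevalence of chronic pain will be reported, with a 95% confidence interval". No interval method is named. Logistic and linear regressions follow, with age and gender as the only named adjustments.

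**Limitations.** Non-random recruitment is acknowledged. Clustering is not mentioned.

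**The concern.** The sample-size formula treats the 288 responses as independent draws from 86,424 adolescents. The design delivers groups of classmates from a handful of schools. Classmates share an age band, a catchment area and a teacher, and pupils of one school share more than pupils drawn at random from four cantons. If chronic pain is even slightly more alike within these groups than between them, 288 responses carry less information than 288 independent ones.

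The quantity affected is the primary one, the point prevalence and its confidence interval. The Discussion presents the study as giving a more precise estimate than earlier Swiss work, so precision is part of its purpose. An interval computed without regard to the grouping would be too narrow and would cover the true prevalence less often than 95%.

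**Working it through.** **Inputs from the article:** prevalence p = 0.25, half-width d = 0.05, 95% confidence (z = 1.96), N = 86,424, response rate 80%, four schools (all from Sample size and Setting).

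**Inputs assumed, because the article does not give them:** 20 responding pupils per class; ICC of 0.005 to 0.05 at class level and 0.01 to 0.03 at school level. Responses per school: 288 / 4 = 72.

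**Step 1: reproduce the plan's figure.**
- n = z² p(1 − p) / d² = 1.96² × 0.25 × 0.75 / 0.05² = 288.1.
- With the finite-population correction: 288.12 / (1 + 288.12 / 86,424) = 287.2, rounded up to 288.
- Inclusion target: 288 / 0.80 = 360.

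Both figures reproduce, and only with a design effect of exactly 1.

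**Step 2: allow for clustering.**
- Design effect: DE = 1 + (m − 1) × ICC.
- Half-width: 1.96 × √(0.1875 × DE / 288), which is 5.0 × √DE points.
- Coverage of a 95% interval that ignores clustering: 2Φ(1.96 / √DE) − 1.
- Responses needed for ±5 points: 288 × DE; to include: that figure / 0.80.

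| Cluster | ICC | DE | Half-width (points) | Coverage if ignored | Responses for ±5 | To include |
|---|---|---|---|---|---|---|
| Class, m = 20 | 0.005 | 1.09 | 5.2 | 94% | 316 | 395 |
| Class, m = 20 | 0.01 | 1.19 | 5.5 | 93% | 343 | 429 |
| Class, m = 20 | 0.02 | 1.38 | 5.9 | 90% | 398 | 497 |
| Class, m = 20 | 0.05 | 1.95 | 7.0 | 84% | 562 | 702 |
| School, m = 72 | 0.01 | 1.71 | 6.5 | 87% | 493 | 616 |
| School, m = 72 | 0.02 | 2.42 | 7.8 | 79% | 697 | 872 |
| School, m = 72 | 0.03 | 3.13 | 8.8 | 73% | 902 | 1,127 |

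At a class-level ICC of 0.01, the 429 to include already exceed both the target of 360 and the roughly 400 pupils in the confirmed schools.

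**Step 3: few schools.** If schools are the primary units, four of them leave 3 degrees of freedom and the quantile is 3.18 instead of 1.96. The half-width is then 3.18 × √(0.1875 × 1.71 / 288) = ±10.6 points at ICC 0.01, and ±12.6 points at ICC 0.02.

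**Step 4: regressions.** For a regression coefficient, the variance inflation is roughly 1 + (m − 1) × ICC of the covariate × ICC of the outcome. Age is tied to class, so its ICC is high and the inflation approaches the full DE. Gender and individual COPI-GER scores vary mainly within classes, so the inflation is close to 1. PROMIS-PPIS is collected only from pupils with chronic pain: 0.25 × 20 = 5 per class. The design effect there is at most 1 + 4 × 0.01 = 1.04 to 1 + 4 × 0.05 = 1.20.

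**The case against.** **The size rests on assumptions.** This stands. Neither the ICC nor the class size is in the article, and at ICC 0.005 the loss is about 0.2 points. The article's own prevalence range of 3% to 38% moves the half-width from about ±2.0 to ±5.6 points with no clustering at all. The direction does not depend on these assumptions: any positive ICC widens the interval.

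**This is a condensed article, and a full analysis plan may name a cluster-adjusted method.** This stands for the analysis. A reader might infer that the article specifies an interval and regressions that assume independence. It does not; it is silent on the variance method. The ±5-point figure is different: it is stated here, and no later plan can make it true of 288 clustered responses.

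**Not every analysis suffers.** A reader might infer that all regression standard errors will be too small. Step 4 of the working shows otherwise.

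**Clustering may still be recoverable.** A reader might infer from the demographics list that it could not be handled afterwards. The list does not show that no code exists, and data are exported after each session, so a code may be attachable then. The article does not say, however, that exports are separate files or that one session is one class. Collection began in September 2023, so a code may be harder to recover for pupils already surveyed.

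**Non-random school selection is the larger threat.** This is a fair point, and the Limitations section acknowledges it. Cluster adjustment does not cure selection bias, but that is no reason to overstate precision as well. Four is also a provisional number: more schools would reduce the school-level effect but leave the class-level one.

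**Conclusion.** The precision statement in Sample size is wrong as written for this design. The arithmetic is right, but it describes a simple random sample. On the stated assumptions, 288 responses give about ±5.5 to ±7.0 points with class clustering alone (classes of 20, ICC 0.01 to 0.05). They give about ±6.5 to ±8.8 points if schools differ (72 each, ICC 0.01 to 0.03), and ±10.6 or more if the small number of schools is also reflected in the quantile. The coverage figures apply to a reported interval that ignores clustering, not to the illustrative 20% to 30% used for planning.

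The direction is certain for any positive ICC; the size is not known. For the prevalence interval and the regressions, the point is that no allowance for clustering appears, not that a wrong method has been specified. The documents do not support a claim that every regression is materially affected or that the grouping is lost.

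**What to change.** 1. **Restate the precision.** Say that ±5 points holds under simple random sampling only, and give the wider range under stated ICC assumptions at both class and school level. Quoting only the class-level ±5.5 to ±7.0 would omit between-school variance.
2. **Keep the grouping.** Attach a coded school and class or session identifier to each record wherever this is still possible. Withhold or scramble it in the open dataset.
3. **Report a cluster-adjusted prevalence interval and the observed ICC.** State the target of inference. Treating schools as strata or fixed effects limits the interval to the participating schools. Inference to Central Switzerland, the stated target, needs between-school variance, which four schools estimate poorly.
4. **Account for class in the regressions**, with a random intercept or GEE and a small-sample correction. Note that this matters mainly for covariates that vary between classes, such as age, and is likely to change little for gender, COPI-GER or the PROMIS-PPIS models limited to pupils with chronic pain.

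The cost is one coded field, a few lines of analysis and a less favourable precision statement. The code is the time-critical part, because collection was due to end in January 2024 and class membership may be hard to recover from anonymised records.

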### Timeline

Preparations for data collection and information events took place in August and September 2023. Data collection commenced in September 2023 and is expected to be completed in January 2024. Data analysis will begin on completion of the data collection.

## Discussion

This study will attempt to provide a more precise estimate of the prevalence, characteristics and impact of chronic pain in adolescents aged between 11 and 17 years in Central Switzerland compared to previous research [15]. Specifically, this study will provide estimates of the severity, duration, and location of chronic pain in adolescents and the extent to which it impacts on their physical, psychological and social functioning.

Furthermore, the study will assess the adolescents’ knowledge and beliefs about pain. Unhelpful beliefs and misconceptions about pain may contribute to maladaptive behaviours and the development of chronic pain. Identifying specific misconceptions about pain could inform future studies that design interventions to target these misconceptions and better align adolescents’ understanding of pain with contemporary pain science. Such understanding may ultimately contribute to the prevention and treatment of chronic pain in adolescents. Future projects can utilize the findings to design interventions that target and rectify these misconceptions.

### Limitations

This study has several potential limitations. One limitation is the non-randomized recruitment process. It should be noted that recruiting schools to participate in research studies can be challenging. However, the study aims to ensure a sufficient sample size to make valid inferences about the population.

Even though the observational study design is the most appropriate design to answer the research questions, this design is prone to several internal validity problems, such as self-report bias, selection bias, information bias, and reporting bias [55].

The potential limitations of self-reporting when using PROMs to measure our outcomes of interest are acknowledged [56]. Specifically, the pupils are asked how long they have been in pain, which could lead to a recall bias. To reduce this bias, a reference point will be discussed with the teacher beforehand to help the adolescents accurately estimate the duration of the past three months. Furthermore, age- appropriate validated questionnaires will be utilized.

The study outcomes are based, in part, on existing pain-related instruments used in similar studies (e.g. pain intensity, pain locations). The reliability and validity of our exact instrument has not been tested but is inferred from the available psychometric data upon which the original questionnaires are based.

The scope of our study does not enable us to collect data on medication usage, the influence of any perceived school-related pressures, the prevalence of chronic pain among parents or socio-economic status. The extent to which these variables might confound our findings is not known.

The selection and recruitment procedure could lead to a selection bias, towards those with more severe or chronic pain. To reduce this bias, the project will use a standard recruitment process to ensure a representative sample of the population. Information bias will be limited by using the most valid and reliable outcome measures available. In order to minimise reporting bias we have published this study protocol and will report any and all deviations from the protocol. Finally, our study will recruit participants from schools in Central Switzerland and as such our findings may not generalise to other geographical locations.

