Parents/legal guardians and pupils will be informed that study participation is entirely voluntary and that their children are free, without justification, to decline to participate or withdraw from the study at any time. Before data collection commences, the PI will explain the procedure in plain simple language to the adolescents again and screen them for eligibility to ensure that participants meet the inclusion criteria. The screening procedure will involve verbally asking the child if they can read and write in the German language. All pupils receive the same online link. As an additional verification of willingness to participate, adolescents can decide to complete the survey or a reading substitute task. If a participant chooses the reading substitute task, a text previously chosen by the teacher will appear on the screen instead of the survey.

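### The Limitations section claims a representative sample and valid population inference, but the volunteer recruitment it describes cannot deliver either

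*Protocol article*

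**What the plan says.** In the Limitations section the article concedes that "One limitation is the non-randomized recruitment process", and a few lines later that selection could run towards pupils with more severe or chronic pain. It gives two reassurances. On the non-random recruitment, it says that "the study aims to ensure a sufficient sample size to make valid inferences about the population". On the selection bias, it says: "To reduce this bias, the project will use a standard recruitment process to ensure a representative sample of the population".

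Other sections show how pupils enter the study:

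- **Schools** (Recruitment, Setting): invited by mail, free to withdraw at any time, and replaced by other invited schools from the same region. Four schools with about 400 pupils had provisionally confirmed.
- **Teachers** (Recruitment): classes are reached through teachers who agree to support the study, and they too may withdraw.
- **Pupils** (Recruitment): "adolescents can decide to complete the survey or a reading substitute task".

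The primary result is described in one sentence of the Statistical analysis plan section: "An estimate of the point prevalence of chronic pain will be reported, with a 95% confidence interval". The Aims and objectives section makes this the prevalence among 11- to 17-year-olds in Central Switzerland, and the Sample size section ties it to a population of 86424 adolescents in four cantons.

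**The concern.** The two reassurances are stated as safeguards for the primary objective, and neither can do that work. A standard procedure makes the approach to schools and pupils uniform. It has no influence on which schools accept or which pupils choose the survey. A larger sample reduces random error around whatever value the recruited pupils are expected to give. If that value differs from the population value, more pupils only make the interval tighter around the wrong figure.

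A reader who trusts these sentences will take the 95% confidence interval as covering the uncertainty about prevalence in Central Switzerland. It covers sampling error only. Two further sources of error lie outside it: the age and gender mix of the classes that happen to take part, and participation that depends on having pain.

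**Working it through.** **1. Reproduce the planned precision.** Inputs from the Sample size section: prevalence 25% ("Assuming that 25% of our sample have chronic pain"), precision 5 points, population 86424, response 80%.

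- Single proportion under simple random sampling: n₀ = 1.96² × 0.25 × 0.75 / 0.05² = 288.1.
- With the finite population correction: n = n₀ / (1 + (n₀ − 1)/86424) = 287.2, rounded up to 288. This agrees with the plan.
- Inflation for response: 288 / 0.80 = 360. This agrees with the statement "With an estimated response rate of 80%, it is aimed to include 360 adolescents".
- Half-width at 288: 1.96 × √(0.25 × 0.75 / 288) = 5.0 points.

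The arithmetic is right, but the formula assumes a simple random sample of the 86424, which is not how pupils are recruited.

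**2. What more pupils would do.** At n = 360 completed responses the half-width would be 1.96 × √(0.25 × 0.75 / 360) = 4.5 points. Any selection bias would be unchanged.

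**3. Non-response among invited pupils.** Let r be the response rate, p_resp the prevalence in responders and p_nonresp the prevalence in non-responders. Then p = r × p_resp + (1 − r) × p_nonresp. With r = 0.80 and p_resp = 25% this is p = 20% + 0.20 × p_nonresp. The documents give no value for p_nonresp, so all the values below are assumed.

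| Assumed p_nonresp | Prevalence among invited pupils |
|---|---|
| 0% (logical bound) | 20% |
| 10% | 22% |
| 15% | 23% |
| 25% | 25% |
| 35% | 27% |
| 50% | 30% |
| 100% (logical bound) | 40% |

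In the direction the protocol names (fewer non-responders with pain), 10–15% puts the responder figure 2–3 points too high.

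**4. The same question from the participation side.** Suppose true prevalence is 25% and pupils with pain are RR times as likely to take part as pupils without. Expected observed prevalence = 0.25 × RR / (0.25 × RR + 0.75). Coverage is that of the nominal 95% interval at n = 288. The RR values are assumed.

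| RR | Observed prevalence | Shift (points) | Coverage |
|---|---|---|---|
| 0.8 | 21.1% | −3.9 | about 62% |
| 0.9 | 23.1% | −1.9 | about 88% |
| 1.0 | 25.0% | 0 | 95% |
| 1.1 | 26.8% | +1.8 | about 89% |
| 1.2 | 28.6% | +3.6 | about 73% |
| 1.25 | 29.4% | +4.4 | about 62% |

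Steps 3 and 4 concern pupils within participating schools only. Selection between schools is not included.

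**5. What the described analysis covers.** The sensitivity analyses are illustrated by exclusions and outliers. The Missing data section deals with missing values variable by variable. Neither, as described, addresses who entered the sample.

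**The case against.** The strongest reply is that the protocol hides nothing. It names non-random recruitment, selection bias and its likely direction, and it limits generalisation to other regions. It speaks of reducing the bias, and the sample-size sentence is framed as an aim. This stands as far as disclosure goes: the fault is the claimed cure, not concealment.

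Several design features also limit self-selection on pain. Teachers introduce the study in class time, every pupil gets the same link, the investigator and teacher are in the room, and pupils without pain also have a questionnaire to complete. These make strong pain-related participation less likely within a class. They do not remove it, and they do nothing about which schools and teachers agree.

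A reader might infer that the prevalence will be left unweighted. The documents do not support that. The article is silent on weighting, its list of sensitivity analyses is open-ended, and such detail is often left to a fuller plan. The silence by itself is no fault.

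A reader might also expect weighting to cure the problem. It would not. Adjusting for age and gender corrects the mix on those variables only and leaves pain-related participation untouched. The article gives only the single total of 86424, with no breakdown, and canton is not a listed questionnaire item. Seven ages by two genders gives 14 cells, about 20 pupils each at 288 responses. Adding four cantons gives 56 cells of about 5, too sparse to use.

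Finally, the article does not say that reading-task choices are recorded. Its Data collection section has excluded pupils also steered to that task, so a plain count would mix ineligible pupils with refusers.

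**Conclusion.** The point holds as a wrong statement about the primary estimate. Neither a standard recruitment process nor a sufficient sample size makes a sample of volunteer schools and self-selecting pupils representative, and the same section admits the selection that these are said to resolve. This conclusion rests on the text and needs no assumed figure.

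The size is illustrative. A shift of 2–3 points follows if 80% respond, 25% of responders have chronic pain and 10–15% of non-responders do. Participation ratios of 1.1 to 1.25 give +1.8 to +4.4 points. These shifts lie within the planned 5-point precision but are large enough to matter beside it. The documents do not show that such a bias will occur, and the opposite direction is possible, so the figures should not be read as a predicted error.

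**What to change.** 1. **Restate the claim.** Replace both sentences in the Limitations section with a statement that this is a volunteer sample of schools and pupils, and that the 95% confidence interval covers sampling error only, not selection.
2. **Show a standardised figure beside the crude one.** Report prevalence directly standardised to the age distribution of the 11–17 population behind the 86424, and to gender where population counts exist. The breakdown must be obtained from the population source. Do not use canton cells. State that the result corrects age and gender mix only, not pain-related participation.
3. **Report participation and a sensitivity line.** Give counts at school and pupil level, separating eligible refusers from ineligible pupils given the reading task. First confirm how that choice can be recorded. Then report p = r × p_resp + (1 − r) × p_nonresp, with p_nonresp at several assumed multiples of p_resp on both sides of 1. For example, with r = 0.80 and p_resp = 25%, multiples of 0.5, 0.75, 1, 1.25 and 1.5 give 22.5%, 23.75%, 25%, 26.25% and 27.5%.

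The cost is a little more analysis, one request for population counts, some record-keeping in class and a somewhat wider interval for the standardised figure. No additional pupils are needed.
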